#### 5.7 Description of the intervention

From week 8 after delivery, measurements will be taken and the intervention of the two groups will be carried out. First, measurements will be taken, which will be carried out in one day with the procedure explained in the previous point. Afterwards, the participants will carry out the intervention in each of the groups for 6 weeks and then, once these 6 weeks have passed, the final measurements will be taken. None of the abdominal strengthening programs are offered as a regular service to women in the postpartum period in primary care centers.

##### *Description of the intervention*

*Group 1:* Classic abdominal strengthening exercises (curl-ups, sit-ups and leg-rise), balance exercises, general mobility and upper limb strengthening exercises.

*Group 2:* Hypopressive abdominal exercises, balance exercises, general mobility and upper limb strengthening exercises.

In both groups the exercise programs will have a duration of 6 weeks, with a timing of 2 days per week (1 hour per session), making a total of 12 sessions. The interventions will be carried out in the Navia Health Center, when there is availability of space and prior authorization of the Management of the Health Area of Vigo.

5.8 Timeline and expected completion date. Distribution of tasks among the members of the research team.

The study is expected to begin and end in 2022, provided that health conditions permit and the ethics committee approves. The distribution of tasks of the investigators is as follows:

- [name]: Theoretical development of the project and organization of the rest of the researchers. Randomization of the participants to the treatment groups. Statistical analysis of the data and participation in the writing of the research article derived from this research.
- [name]: In charge of carrying out the exercise program in the classical abdominal strengthening group. Participation in the writing of the article derived from this research.
- [name]: In charge of carrying out the exercise program in the hypopressive abdominal exercises group. Participation in the writing of the article derived from this research.
- [name]: Participation in the theoretical development of the project, in the statistical analysis of the data and in the writing of the article derived from this research. In charge of carrying out the evaluations (pre and post intervention) through ultrasound measurements.
- [name]: Recruitment of participants and collection of obstetric variables.
- [name]: Recruitment of participants and collection of obstetric variables.
- [name]: Recruitment of participants and collection of obstetric variables.
- [name]: Recruitment of participants and collection of obstetric variables.
- [name]: Recruitment of participants and collection of obstetrical variables

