## **4. Type of study**

- Definition of study design: Blinded, parallel group clinical trial.

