## 5.6 Primary and secondary variables

The difference in inter-straight distance (DIR) before and after the intervention will be used as the treatment effect variable. The researcher who will carry out the measurements will be blinded and will not know to which group each participant belongs. The measurements will be carried out at the Navia Health Center, when space is available and with prior authorization from the Management of the Vigo Health Area.

- Measurement of DIR: Participants will be positioned in the supine position with knees bent at 90° with feet resting on the table and arms alongside the body. After being instructed to perform an abdominal crunch, subjects are asked to separate the head and elevate the shoulders until the scapula detaches from the table.

Ultrasound images will be recorded with an ultrasound scanner (GE Logic-e; 4-12 MHz, 39 mm linear transducer; B-mode), in a supine resting position and a muscle activation position (isometric contraction), 2 cm and 5 cm above the umbilicus.

To ensure that the two DIR measurements (2 cm and 5 cm above the umbilicus) are taken at the same location, the skin is marked with a water-soluble pen.

Ultrasound image collection will be performed immediately at the end of exhalation, as determined by visual inspection of the abdomen following the recommendations of Teyhen et al. (27) Special attention will be paid to the pressure exerted on the ultrasound probe on the patient to avoid reflexive response of the abdominal musculature (28).

For ultrasound image acquisition, the lower edge of the transducer will be placed over the mark made and moved laterally until the medial edges of both anterior rectus muscles can be visualized. The orientation of the transducer will be adjusted to

optimize image visualization. The collected ultrasound images will be exported to DICOM format for further measurement, analyzed by the same investigator, using a customized Matlab code (Image Processing Toolbox, Mathworks Matlab, USA) following the procedures described by Mota et al. (28). There is a good intra-evaluator reliability in DIR ultrasound images, with confidence interval values higher than 0.90(27).

These will be collected as independent variables:

- Group to which the patient is randomized (hypopressive abdominal exercises group and classic abdominal exercises group).

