## 9. Data collection notebook

Data collection will be carried out in an Excel document. The column of the group to which the participants belong will be covered at the end of the study by the principal investigator, since the researcher conducting the evaluation will be blinded during data collection and when entering the data in the Excel document. The time of data collection is attached.

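### Section 4 says only that the trial is blinded; the blind covers the ultrasound assessor through data entry, while the analysis is shared by the randomizer and the assessor with no masking described

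*Protocol*

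**What the plan says.** The design statement in section 4 of the protocol is "Definition of study design: Blinded, parallel group clinical trial". It does not say who is blinded.

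Section 5.6 gives blinding to one role: "The researcher who will carry out the measurements will be blinded and will not know to which group each participant belongs". Section 9 gives the period: "the researcher conducting the evaluation will be blinded during data collection and when entering the data in the Excel document". On group assignment, section 9 says: "The column of the group to which the participants belong will be covered at the end of the study by the principal investigator". The verb in that sentence reads as a translation of filled in.

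Section 5.8 divides the work. After developing the project, one team member has the tasks "Randomization of the participants to the treatment groups. Statistical analysis of the data and participation in the writing of the research article". Another entry reads "Participation in the theoretical development of the project, in the statistical analysis of the data and in the writing of the article", and the same entry continues: "In charge of carrying out the evaluations (pre and post intervention) through ultrasound measurements". Two further members each run the exercise programme of one arm.

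**The concern.** A reader who meets the bare label in section 4 cannot tell whether it covers participants, instructors, assessor or analysts. The protocol supports it for the assessor only, and only up to data entry.

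The second part concerns the analysis stage. As the tasks are divided, both people named for the statistics can know the arm while they work: one because they did the randomizing, the other because the comparison needs the completed group column. The study hypothesis in section 2 is directional, in favour of hypopressive exercise. If the DIR measure or the test is chosen at that stage, the choice can be influenced by knowing which arm it helps. What is at stake is the credibility of the primary comparison and an accurate description of the design.

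**Working it through.** No figure in the protocol bears on this point, so the check sets the sections side by side, role by role.

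| Role | What the protocol says | Blind? |
|---|---|---|
| Participants | Openly different abdominal exercises in the two arms, no sham or masking (5.7) | No, by inference from the exercises |
| Instructors | One person per arm (5.8) | No, each necessarily knows the arm |
| Ultrasound assessor | Blind while measuring (5.6) and while entering data (9) | Yes, to the end of data entry |
| Randomizer, also analyst | Both tasks in one entry (5.8) | No |
| Assessor as analyst | Shares the statistical analysis (5.8) | None stated for this stage |

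**Step 1: order of events.** The assessor enters the data blind, and the group column is completed at the end of the study (section 9). The natural reading is that the DIR values are in the file before group appears. Section 5.6 has the images exported and measured off-line, but section 9 implies that this too is finished before the column is filled.

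**Step 2: what the analysis needs.** Section 5.9 bases the main analysis on the pre-post difference in DIR compared between groups. That needs the group column. Section 9 does not say whether the column will hold group names or codes, and no section describes a masked analysis. That the assessor analyses with group visible is therefore an inference from sections 5.8 and 9 together.

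**Step 3: what is still open at that point.** Section 5.6 records DIR at 2 cm and 5 cm above the umbilicus, each at rest and in contraction: 2 sites × 2 states = 4 measures. None is named as the primary one. Section 5.9 makes an ANOVA of the difference conditional on a Shapiro-Wilk result, names a repeated measures analysis for the main comparison, and leaves Pearson or Spearman to be chosen for the obstetric variables.

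**Step 4: how much freedom this is.** For one DIR measure with complete pre and post values, the group-by-time F of a repeated measures ANOVA equals the F of an ANOVA on the change. Naming both therefore adds little unless site or contraction state enters as a further factor. Most of the freedom lies in the four measures, and then in what follows the normality test.

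**The case against.** The strongest reply is that the label is unqualified, not false. Sections 5.6 and 9 state plainly who is blind, and no section claims blinding of participants, instructors or analysts. Open delivery is unavoidable when two visibly different exercise programmes are compared, and the outcome is an ultrasound distance read by a blinded assessor, not a self-report. All of this stands. A reader might infer that section 4 claims a protection the trial lacks; the documents support only that it fails to say who is covered.

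A reader might also infer that DIR values could be re-read or corrected once the arm is visible, and attach a size to that, such as the effect of a few altered readings in small arms. The protocol describes no such re-reading, and section 9 has the values entered blind before group is added. Any figure would rest on an invented edit and would not estimate bias, so none is given here.

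A third reply is that file locks, coded labels and masked analysis usually belong in an SAP or a data-management document, which may exist. That is fair for their absence alone, and the same holds for a fallback test for non-normal data. It does not dispose of the point, because the protocol itself fixes who randomizes, who analyses and when the group column is filled, and that arrangement is what leaves the analysis exposed.

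Finally, the assessor is not an outsider to the data either. That is so, but an assessor working on coded groups would still be blind to which arm is which; the randomizer, who made the assignments, may not be.

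**Conclusion.** The point holds in limited form. The protocol should say that the trial is assessor-blinded, and it gives the statistical analysis to the person who randomizes together with the assessor, with no masking described. The measurement of DIR is probably sound. The exposure is confined to the choice among four DIR measures, and among tests, by analysts who know the arm.

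The size cannot be expressed as a number from the protocol. This is an inexpensive improvement, not a fault that invalidates the trial.

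The conclusion rests on three assumptions: that participants and instructors know their arm, which follows from the interventions; that the group column is completed before the between-group analysis and is not coded; and that all image readings precede it. If an SAP names the primary DIR measure and the tests in advance, the analysis part shrinks further and the wording of section 4 is what remains.

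**What to change.** - **Section 4:** write that the trial is assessor-blinded and that participants and instructors are not blinded. Add analyst-blinded only if the next two steps are adopted.
- **Section 9:** complete all DIR readings and save a dated, read-only copy of the Excel file before the group column is filled. Then fill the column with neutral codes (A and B), the key being held by someone who does no analysis. Either instructor would qualify, since section 5.8 gives them no statistical task.
- **Section 5.8:** have the assessor, already named as an analyst, run the primary between-group analysis on the coded file. The randomizer takes no part in it until the primary result is fixed, and the code is broken after that.

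The cost is wording in three places and one saved file. No extra staff, visit or measurement is needed. The downsides are a short delay before the labels are revealed and a narrower analysis role for the randomizer.

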### 5.9 Statistical analysis plan

The dependent variable (DIR) will be analyzed using standard normality tests (Shapiro-Wilk test) to find the normality criteria (29). In the case of a normal distribution of the data, the difference in DIR will be analyzed through an analysis of variance (ANOVA).

The Pearson or Spearman correlation coefficient will be used for the analysis of obstetric variables and their relationship with the DIR.

The main analysis will be based on the difference in DIR pre-post intervention and the comparison between groups by means of a repeated measures analysis. A significance level of  $p < 0.05$  will be established for all variables.

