## **3. Objectives**

- Main objective: To evaluate the effect of two abdominal strengthening programs (classical abdominal exercises *versus* hypopressive abdominal exercises) on the inter-straight distance in postpartum women.
- Secondary objectives: To evaluate possible differences on the effect of programs depending on their obstetric history (maternal age, fetal weight, no. of deliveries, weight gain in pregnancy).

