## 5.5 Justification of sample size.

A sample size of 10 participants was established for each group. The estimation of the sample size was based on the study by Sancho et al (10), in which the effect size was between 0.43 and 0.25 of the inter-straight distance for the supraumbilical and infraumbilical measurements. This sample size was calculated using G-Power 3.1 software with an alpha error of 0.05 and a power of 0.95. Considering a loss rate of 30%, a sample size of 14 participants per group was finally estimated.

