- Obstetric variables (maternal age, fetal weight, number of deliveries, weight gain during pregnancy): these variables will be administered by the midwives through their clinical history.

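### The secondary objective asks whether the programs' effect depends on obstetric history, but the planned correlations with DIR contain no comparison between arms and so do not test it

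*Protocol*

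**What the plan says.** The secondary objective in section 3 is "To evaluate possible differences on the effect of programs depending on their obstetric history", and the history is listed there as maternal age, fetal weight, number of deliveries and weight gain in pregnancy. Section 5.6 lists the same four as independent variables, alongside the randomized group.

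Section 5.9 contains three analysis statements:

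- An ANOVA of the difference in DIR if the data are normal.
- For the obstetric variables: "The Pearson or Spearman correlation coefficient will be used for the analysis of obstetric variables and their relationship with the DIR".
- A main analysis of the pre-post difference in DIR, with "the comparison between groups by means of a repeated measures analysis". The obstetric variables do not appear in it.

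Section 5.9 does not say whether the DIR to be correlated is baseline, final or change, which site or contraction state is meant, or whether the two arms are pooled. Section 5.6 says of the outcome: "The difference in inter-straight distance (DIR) before and after the intervention will be used as the treatment effect variable". It describes measurements at two sites above the umbilicus, at rest and in contraction, and names none of the four as primary.

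**The concern.** A question about differences in the effect of programs according to history is a question about interaction: does the contrast between hypopressive and classic exercises change with, say, maternal age? A correlation of age with DIR describes how age goes with DIR among the women analysed. That is a prognostic association. It can be strong when age has the same influence in both arms and the contrast between programs is constant. It can be near zero when age acts in opposite directions in the two arms and the contrast varies a great deal.

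Followed as written, the plan produces coefficients that leave the secondary objective unanswered. The primary comparison is not affected.

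**Working it through.** **1. Objective against method.** The objective needs a quantity that involves both the group and the obstetric variable. In section 5.9 the correlation involves the obstetric variable without the group, and the main analysis involves the group without the obstetric variable. No planned analysis contains both.

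**2. Sample size used.** Section 5.5 states: "A sample size of 10 participants was established for each group", and 14 per group after allowing for losses. The figure of 10 can be reproduced for the main comparison by taking the effect size as Cohen's f = 0.43 in a within-between repeated-measures ANOVA with two times and an assumed correlation of 0.5. Then λ = f²·N·m/(1−ρ) = 0.43² × 20 × 2 / 0.5 = 14.8, and power is 0.953 at N = 20. The calculation concerns the main comparison only. It is used here just to fix 10 and 14 per arm.

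**3. Illustration.** The slopes are assumptions; the protocol gives none. The covariate is standard normal, the residual SD is 1, there is no mean difference between arms, and tests are two-sided at 0.05. The interaction test is the test of the group × covariate term in a linear model. Share of simulated trials with p < 0.05, 10 per arm:

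| Slopes in the two arms | Modification? | Pooled correlation | Interaction test |
|---|---|---|---|
| 0.6 and 0.6 | none | 68% | 5% |
| 0.6 and −0.6 | strong | 7% | 60% |
| 0.6 and 0 | yes | 23% | 20% |

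At 14 per arm the first row becomes 83% and 5%, and the second 8% and 78%. A version set up in correlations, with 0.5 in one arm and 0 in the other, gives 26% and 25% at 14 per arm.

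*Rough check of the first row.* A slope of 0.6 with residual SD 1 is a correlation of 0.6/√(1 + 0.36) = 0.51, whose Fisher z is 0.57. With 20 women pooled, 0.57 × √17 = 2.35, and Φ(2.35 − 1.96) = 0.65, close to the simulated 68%.

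**4. Arms analysed separately.** With the same slope of 0.6 in both arms, each arm of 10 reaches significance in about 35% of trials. The chance that exactly one does is about 2 × 0.35 × 0.65 = 0.46, and simulation gives about 46%. At 14 per arm it is about 50%. A significant coefficient in one arm and not in the other is therefore a common result when there is no modification.

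**5. What an interaction analysis can deliver.** With covariate SD 1 in each arm and residual SD 1, the 95% CI half-width for the difference in slopes is about t × √(2/(n−1)). For 10 per arm this is 2.12 × √(2/9) = 1.00; for 14 per arm it is 2.06 × √(2/13) = 0.81. In terms of power at 10 and 14 per arm: within-arm correlations of +0.5 and −0.5 give 57% and 75%, +0.5 and 0 give 17% and 25%, and +0.3 and −0.3 give 22% and 31%.

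**6. Number of tests.** Four variables on one DIR measure, tested independently at 0.05, give 1 − 0.95⁴ = 0.19.

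**The case against.** *The objective may mean something else.* Section 5.6 calls the pre-post difference the treatment effect variable. A reader could then take the objective as asking whether a woman's change varies with her history, and a correlation of change with history addresses that. The reading is possible, but it strains section 3, which speaks of differences in the effect of the programs in a trial built to compare two of them. Change within one arm also includes whatever would have happened without that program. If this reading is intended, the objective needs rewording.

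*Pooling is not stated.* This stands. A reader might infer that the plan merges the arms and ignores group; section 5.9 does not say so. Correlations run within each arm and compared formally, for example by Fisher z, would test the objective about as well as an interaction term. But the protocol states no such comparison, and without one the separate coefficients mislead as in step 4.

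*The contrast of 7% with 60% is a worst case.* This also stands. Exact cancellation is the hardest case for a pooled correlation. With slopes of 0.6 and 0 the two tests reject about equally often, and with 0.3 and 0 both reject in about 9%. A reader might infer that the correlation always misses modification; it does not. Equal rejection rates still do not make it a test of modification, because it rejects far more often when there is none.

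*Multiplicity.* A reader might multiply four variables by four DIR measures and quote 1 − 0.95¹⁶ = 56% for at least one false positive. Section 5.9 does not say that all 16 pairs will be tested, and four measures on the same woman are not independent. The documents do not support that figure.

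*Reporting.* Nothing in the protocol says that the correlations will be published as differences in program effect. That is a risk, not a stated intention.

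**Conclusion.** The point holds as a mismatch between objective and analysis. Section 3 asks about effect modification, and section 5.9 fixes a method that does not test it under either reading of how the arms are handled. This is not a detail left to a separate SAP, because the protocol itself names the method.

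The mismatch follows from the text alone. The percentages only illustrate it, and they rest on assumed slopes, a normal covariate (a poor fit for number of deliveries, which is a small count) and 10 to 14 women per arm. The sturdiest of them is the case without modification: about 68% significant pooled correlations against 5% for the interaction test, or about 46% of trials with exactly one significant arm. The gain in detecting real modification ranges from large, with opposite slopes, to none, with slopes of 0.6 and 0.

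The consequence is limited to a secondary objective that can only be exploratory at this sample size.

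**What to change.** In section 5.9, replace the correlations as the analysis of the secondary objective. For each of the four obstetric variables, fit a linear model of DIR (post-intervention or change) with group, baseline DIR, the obstetric variable and group × obstetric variable. With baseline DIR in the model, the two choices of outcome give the same interaction estimate.

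Use one DIR measure, with site and contraction state chosen in advance. Section 5.6 names none as primary, so that choice has to be made and written down first. Report the interaction estimate with its 95% CI and label it exploratory; with four such tests, quote the chance of about 19% of at least one false positive if they are independent. Any correlation that is kept should be described as a prognostic association, stating which DIR it uses and whether the arms are pooled.

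If only the association between history and change is of interest, reword the objective in section 3 instead.

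The cost is the analysis wording and the choice of one DIR measure; no new data are needed. The drawback is that intervals will be wide at 10 to 14 per group, and all but very large modification will probably go undetected.

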#### 5.4 Allocation/randomization procedure

A simple randomization will be performed for each of the groups. Once consent has been obtained, the patients will be randomized to each of the groups according to a list of random numbers previously generated.

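### The main analysis compares unadjusted pre-post DIR change although baseline DIR is measured; adjusting for baseline would guard against chance imbalance and, at moderate pre-post correlation, gain precision

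*Protocol*

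**What the plan says.** Protocol section 5.6 defines the outcome as a change: "The difference in inter-straight distance (DIR) before and after the intervention will be used as the treatment effect variable". Section 5.9 builds on that change: "The main analysis will be based on the difference in DIR pre-post intervention and the comparison between groups", the latter "by means of a repeated measures analysis". It also says, after a Shapiro-Wilk test of DIR: "In the case of a normal distribution of the data, the difference in DIR will be analyzed through an analysis of variance (ANOVA").

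Baseline DIR is available for every woman who starts. Section 5.7 says "First, measurements will be taken, which will be carried out in one day", and "once these 6 weeks have passed, the final measurements will be taken". So there is one value before and one after treatment for each DIR measurement. Section 5.6 plans four of these: two sites above the umbilicus, each at rest and in contraction.

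No section names baseline DIR as a covariate. Section 5.4 allocates without stratification: "A simple randomization will be performed for each of the groups". Section 5.5 sets 10 women per group, or 14 after allowing for 30% loss.

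**The concern.** With two time points, the group-by-time test of a repeated measures analysis is the same test as a two-sample comparison of change scores. Both subtract the whole of the baseline value, which assumes that a woman who starts 1 mm wider is expected to finish 1 mm wider. When the pre-post correlation is below 1 and the spread is similar at both times, the expected difference at the end is smaller than that. The arm that happens to start wider then appears to have improved more, for reasons unrelated to the exercises.

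Two things are at stake. One is precision, which matters with 20 to 28 women. The other is how far the estimate in this one trial can be trusted if simple randomization leaves the arms unequal at baseline. Both can be addressed with data that the protocol already collects.

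**Working it through.** **Inputs.** From section 5.5: 10 evaluable women per group (N = 20), 14 per group with losses, alpha 0.05, power 0.95, effect sizes 0.43 and 0.25. From section 5.7: one baseline and one final measurement. Not in the protocol: the pre-post correlation rho, taken here as 0.3 to 0.9. The reader reliability above 0.90 in section 5.6 concerns image measurement and is not the correlation across the six-week programme. I also assume equal SDs at both times and a two-sided test.

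**The plan's own figure.** Section 5.5 does not say what type of effect size is meant. Reading it as Cohen's f for a group-by-time interaction with 2 groups, m = 2 times and rho = 0.5:

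- lambda = N·m·f²/(1 − rho) = 20 × 2 × 0.43²/0.5 = 14.79, on 1 and 18 df. Power is 0.953, so 10 per group is reproduced.
- With f = 0.25, lambda = 20 × 2 × 0.25²/0.5 = 5.00 and power is 0.562.

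The stated sample size therefore fits the change-score test, with rho = 0.5 as one setting that yields it.

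**Precision.** In units of the DIR variance, the change score has variance 2(1 − rho). Final DIR adjusted for baseline has variance 1 − rho². The large-sample ratio is (1 − rho²)/[2(1 − rho)] = (1 + rho)/2. Estimating the slope in a small trial multiplies this by 1 + 1/(N − 4) = 17/16 = 1.0625 at N = 20.

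| rho | (1 + rho)/2 | × 1.0625 | simulated ratio, 10 per arm | ANCOVA power where change score has 0.80 |
|---|---|---|---|---|
| 0.3 | 0.65 | 0.69 | 0.71 | 0.92 |
| 0.5 | 0.75 | 0.80 | 0.79 | 0.88 |
| 0.7 | 0.85 | 0.90 | 0.91 | 0.84 |
| 0.9 | 0.95 | 1.01 | 1.02 | 0.79 |

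Formula and simulation agree to within simulation error. The break-even point solves (1 + rho)/2 × 17/16 = 1, so rho = 32/17 − 1 = 0.88. Above that, adjustment costs slightly more than it returns.

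**On the plan's own effect sizes, at rho = 0.5 and N = 20.** Dividing lambda by 0.75 × 1.0625 = 0.797 and using 1 and 17 df:

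- f = 0.43: 14.79/0.797 = 18.56; power rises from 0.953 to 0.982.
- f = 0.25: 5.00/0.797 = 6.27; power rises from 0.562 to 0.656.

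**Chance imbalance.** The baseline difference between arms has SD √(2/n) in units of the DIR SD.

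- n = 10: P(|difference| > 0.5) = 2[1 − Φ(0.5/0.447)] = 0.26.
- n = 14: 2[1 − Φ(0.5/0.378)] = 0.19.

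Given a baseline difference D, the change-score estimate is shifted by −(1 − rho)·D. For D = 0.5 SD and rho = 0.5 this is −0.25 SD. Among simulated trials with D above +0.5 SD, the average shift of the change score was −0.51, −0.37, −0.21 and −0.07 SD at rho 0.3, 0.5, 0.7 and 0.9. The ANCOVA estimate was shifted by about 0 throughout.

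**Validity.** Simulated with no treatment effect, type I error averaged over randomizations was about 0.05 for both analyses.

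**The case against.** The planned analysis is coherent. It matches the hypothesis of a greater reduction in section 2, it fits the sample size, and it keeps its nominal type I error. The gain from adjustment depends on a correlation that the protocol does not give, and it vanishes near rho 0.9. All of this stands. It limits the point to efficiency and to accuracy in the trial as randomized; it does not remove the point, because over most of the assumed range adjustment does better.

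A reader might infer more than the documents support:

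- **That baseline imbalance goes uncorrected.** It does not. A change score subtracts baseline in full, so the fault is over-correction when the slope is below 1.
- **That a sizeable imbalance is to be expected.** A 26% chance of exceeding 0.5 SD, or 19% at 14 per arm, is a material risk, but most trials of this size would not exceed that threshold, which is itself a choice made here.
- **That the weaker group main effect might serve as the test.** A repeated measures analysis does print that test, but sections 5.6 and 5.9 both rest the treatment effect on the pre-post difference, which points to the interaction.
- **That the main analysis is undefined if normality fails.** Section 5.9 attaches the normality condition to the ANOVA sentence; the sentence on the main analysis carries none. The route for non-normal data may be given in a statistical analysis plan that is not at hand.

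**Conclusion.** The point holds as a worthwhile and nearly free improvement. Sections 5.6 and 5.9 fix an unadjusted change-score comparison although baseline DIR is in hand. At 10 per arm, adjusting for baseline cuts the variance by roughly 30%, 20% and 10% at rho 0.3, 0.5 and 0.7, and by nothing at 0.9. It also removes the dependence of the estimate on chance baseline differences. The figures rest on the assumed range of rho, equal SDs before and after, a linear relation and approximately normal data. Reading the protocol's effect size as Cohen's f is a further assumption, used only for the comparison at the plan's own sample size. The documents do not support calling the planned test invalid or its result biased on average over randomizations.

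**What to change.** In section 5.9, make the primary analysis a linear model of final DIR on group and baseline DIR (ANCOVA), and report the adjusted group difference with its 95% confidence interval. Because section 5.6 yields four DIR values at each visit, either fit the model to each planned measurement with its own baseline, or to the one that the investigators name as primary. Align section 5.6 so that the treatment effect is the baseline-adjusted difference between groups; pre-post change within each arm can stay as description. State that the model is fitted regardless of the Shapiro-Wilk result, with residuals checked afterwards.

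The cost is a change of wording in two sections and one degree of freedom, with no new data. If rho turns out near 0.9 there is no gain, or a loss of about one point of power (0.80 to 0.79).
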